### 5.2.1 RDTs for screening in ISTp

RDTs are used in preference to microscopy for screening in ISTp because they are simple to use; potentially more sensitive at detecting placental malaria than expert microscopy; and allow for a much faster point of care diagnosis than microscopy, especially in busy clinics. The increased sensitivity of the HRP-2 based RDTs, in comparison to microscopy is due to their ability to detect antigens released from parasites in the placenta into the blood stream, even if peripheral parasitaemia is not present. In a study of women giving birth in Ghana, the sensitivity of microscopy of peripheral blood smear to detect placental malaria was 42%, compared with 80% for an HRP-2-based RDT, compared with PCR. The corresponding specificities were 97% for microscopy and 90% for RDT. The lower specificity for RDTs compared with microscopy may have been partly due to the persistence of HRP-2 antigens in the blood, which may remain for up to 14 days after clearance of parasites following treatment.

### 5.2.2 Dihydroartemisinin-piperaquine (DHA-PQ) for ISTp

We will use DHA-PQ as the drug of choice for ISTp. DHA-PQ is an artemisinin combination therapy (ACT) drug combination, each co-formulated tablet consisting of 40 mg dihydroartemisinin and 320 mg piperaquine. WHO now recommends ACTs for the treatment of symptomatic malaria in the second and third trimesters of pregnancy, and many countries are in the process of changing their first line drug in the second and third trimesters of pregnancy from quinine to ACTs, as quinine needs to be given three times daily for seven days and is poorly tolerated.

[name] et al are currently conducting a multicentre trial in Malawi, Burkina Faso, Ghana and Zambia, assessing the efficacy of different ACTs for the treatment of malaria in women who have a positive malaria smear in the second and third trimesters of pregnancy; 'Safe and efficacious artemisinin-based combination treatments for African pregnant women with malaria' (COMREC reference number P03/09/737). The four ACTs being assessed in this trial, approved by the Malawi Pharmacy and Poison Board in May 2010, are dihydroartemisinin-piperaquine (DHA-PQ), artemether-lumefantrine (AL), artesunate-amodiaquine (AQ-AS) and mefloquine-artesunate (MQ-AS). The study has a total sample size of 3,480 participants, including 870 in the DHA-PQ arm (260 of whom are scheduled to receive DHA-PQ in Malawi). Of these regimens, DHA-PQ is the most promising candidate for use in ISTp, despite the possibly longer period post-treatment prophylaxis offered by MQ-AS, because previous trials have shown that it is better tolerated than AQ-AS or MQ-AS, can be given once daily (unlike AL), and provides longer post-treatment prophylaxis than AL or AQ-AS by one to two weeks after each dose. Because ISTp will be given up to three times, this could result in a cumulative difference of three to six weeks post-treatment prophylaxis.

## 6 Objectives

### 6.1 Primary objective

To compare the efficacy of scheduled intermittent screening with malaria rapid diagnostic tests (RDTs) and treatment of RDT-positive women with dihydroartemisinin-piperaquine (ISTp-DP) with intermittent preventive treatment with sulphadoxine-pyrimethamine (IPTp-SP) in the second and third trimesters on adverse birth outcome and malaria infection at term among HIV-negative women protected by insecticide-treated bed nets.

### 6.2 Secondary objectives

#### 6.2.1 Efficacy

To determine if ISTp-DP compared with IPTp-SP in the second and third trimesters of pregnancy is associated with:

- A decrease in the prevalence of placental malaria at delivery
- An increase in the mean duration of pregnancy or a reduction in the prevalence of pre-term birth

- An increase in mean birth weight or a reduction in the prevalence of low birth weight
- A decrease in stillbirths, neonatal deaths or perinatal death
- A decrease in pregnancy loss in the second and third trimesters
- An increase in mean haemoglobin levels or decrease in any anaemia, moderate anaemia and severe anaemia at delivery
- A decrease in the prevalence of peripheral parasitaemia at delivery
- A decrease in the incidence of clinical malaria episodes in pregnancy
- A decrease in the incidence of peripheral parasitaemia in the third trimester of pregnancy
- An increase in mean haemoglobin levels or decrease in any anaemia, moderate anaemia and severe anaemia during the third trimester of pregnancy
- A decrease in the prevalence and incidence of clinical malaria or symptomatic anaemia in infants by seven days and six to eight weeks

### 6.2.2 Tolerability and safety

To evaluate the tolerability and safety of ISTp-DP in the second and third trimesters of pregnancy.

### 6.2.3 Modifiers of efficacy

To explore the possibility of differences in treatment effect by gravidity (first or second pregnancy versus third or subsequent pregnancies) or other groupings relating to the risks of malaria in pregnancy, such as malaria transmission season, location, age, number of intervention visits.

### 6.2.4 Effect on the development of pregnancy-specific immunity

To explore the relative effect of the two different study interventions on markers for pregnancy-specific immunity to *P. falciparum* malaria.

### 6.2.5 Cost-effectiveness and economic burden

- To estimate the cost-effectiveness of ISTp-DP versus IPTp-SP from a societal perspective measuring both provider and user costs
- To use the cost data to populate a model of the economic burden of malaria in pregnancy
- To model the economic cost of scale up of ISTp-DP in Malawi and explore the affordability of the scale up

### 6.2.6 Acceptability, feasibility, implementability and scale up

To explore the acceptability, feasibility, implementability and potential for scale up of ISTp-DP in a busy, routine antenatal clinic setting, using a qualitative assessment.

## 7 Trial design

### 7.1 Overview of design

This will be a two-arm randomized controlled trial conducted at three or more sites in southern Malawi with high levels of SP resistance and high ITN coverage. Enrolment will be stratified by gravidity group (stratified design); one for primi and secundigravidae (G1+2) and one for multigravidae (G3+). The study requires 1665 women overall, including 1155 primi and secundigravidae and 500 multigravidae. It is designed to detect at least a 25% reduction in the primary endpoint consisting of a composite of small-for-gestational age (SGA), low birth weight or preterm birth in women in their first or second pregnancies, and at least a 50% decrease in placental malaria in women in multigravidae. The study will be open label as it will not be possible to blind the participants to their allocation, although where possible laboratory staff undertaking trial-related diagnostic tests will be blinded.

Antenatal clinic sites at Mpemba, Madziabango and Zingwangwa and Chileka will be involved. If less than half the required number of participants is recruited within the first half of the recruitment period, antenatal sites in neighbouring clinics in Blantyre, Zomba or Chikawa districts may be added.

Participants will be HIV-negative pregnant women. They will be screened for eligibility and given information about the study at their first contact with antenatal services before 28 weeks gestation and will be enrolled at 16 to 28 weeks gestation. The study is expected to start in the fourth quarter of 2010 or first quarter of 2011 and recruit for a period of 18 to 30 months, with a further six months follow-up.

Participants will be randomly allocated (see section 17.2 for description of the randomization process) to receive either at least three doses of IPTp with SP or at least three scheduled screenings with an RDT and treatment with DHA-PQ if they are RDT-positive. All participants will be given an insecticide-treated bed net if they do not already have one.

Women enrolled in the trial will make at least three scheduled visits to the clinic spread over the second and third trimesters at least four weeks apart to receive the study intervention approximately mirroring the appointment schedule for 'focussed antenatal care' in Malawi which consists of four scheduled visits. Dating ultrasound scans will be performed to assess gestational age. Women attending early in the second trimester will be asked to make four scheduled visits four to eight weeks apart.

Participants will receive all usual antenatal care according to local policy, including standard clinical examinations, tests and necessary treatment. Women will also be encouraged to attend the study clinic for assessment if they feel unwell during the study period, and to deliver in the maternity wards of the study sites to facilitate collection of delivery outcome data. Participants who deliver at home will receive a home visit within 72 hours (maximum time a week), if possible, to collect the same data as collected for facility births. Participants receiving DHA-PQ will also receive a home visit on day two after the first dose of treatment to encourage and assess their adherence to the study medication, and assess tolerability. Newborns will be seen at approximately seven days and six weeks after delivery, to assess the health of the infant.

In addition to the delivery and birth outcomes, and passive and routine surveillance for illness during pregnancy, blood samples will be taken from all women during the third trimester of pregnancy for later malaria testing by microscopy and PCR. Haemoglobin levels will be tested again in women in the third trimester, and those found to be anaemic will be treated with haematinics according to Government guidelines.

Effects of the different interventions on the development of pregnancy-specific immunity will be evaluated to understand the potential impact of ISTp on development of antibody immunity to malaria, and how this might affect the natural development of gravidity dependent protection from malaria and its complications.

Alongside the main trial will be a study of the feasibility and economics of ISTp. Health facility and exit surveys will be carried out to estimate the costs of the intervention to the health services and households. To capture the costs incurred during the six weeks after delivery, questions about the use of health services will be integrated into the clinical health assessment at six weeks.

Participants will be reimbursed for travel costs to and from the clinic and receive a food allowance. If possible, a study driver will take them home on the day of enrolment to ascertain and record the exact location of their home and address. Women will also be asked for their mobile or home telephone number, if they have one. Attempts will be made to contact women who do not attend scheduled appointments, and to encourage them to attend or to ascertain their reasons for non-attendance.

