#### **7.2.11 Assessment of adverse effects of treatment**

The safety profile of SP in pregnant women is already well documented, and this trial has very limited potential to add significantly to that body of knowledge. There has been less research into the safety of DHA-PQ in pregnancy. In this trial, too few women will receive DHA-PQ to undertake a meaningful analysis of sub-clinical effect, as DHA-PQ will only be provided to women enrolled in the ISTp arm who have a positive RDT result. However, blood samples will be taken at 14 days after treatment and the following tests undertaken to add to the body of knowledge: full blood count; blood haemoglobin levels; total bilirubin, alanine aminotransferase and creatine; and blood DHA-PQ levels. These tests will not be point of care.

Interim placental histopathology results from another trial (IPT-mon) suggest that around 28% (95% CI 19% to 42%) of pregnant women in southern Malawi may experience placental malaria infection. Around 776 participants in this trial will receive ISTp; and since only 20% to 30% of those are likely to be treated with DHA-PQ (as the rest will be RDT-negative throughout) only around 155 to 233 will receive the drug. A larger trial multi-centre study is currently ongoing to assess the safety, efficacy and tolerability of different ACT regimens for the treatment of smear-positive malaria in pregnant women in Malawi and three other African countries; 'Safe and efficacious artemisinin-based combination treatments for African

pregnant women with malaria'. This trial will include 860 women scheduled to receive DHA-PQ and laboratory testing for sub-clinical effects will be undertaken. Data from this trial will add to that knowledge base.

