## 17 Statistical methods

### 17.1 Sample size

The trial will use a stratified design with one strata for primigravidae and secundigravidae and one strata for multigravidae. It is designed to detect a 25% reduction (RR 0.75) in composite adverse birth outcomes (SGA, low birth weight and pre-term birth) in women in their first and second pregnancies with an 90% power and a 2-sided significance level of 0.05, if the rate of placental malaria in the IPT-SP group is similar to that found ongoing observational studies of women receiving routine care in the same area of Malawi. The proposed difference is based on four previous trials of IPTp which jointly reduced low birth weight by 29%. Thus the efficacy of ISTp is expected to be similar to the efficacy of IPTp before the emergence of widespread SP resistance. In the ongoing IPT-mon study in Malawi, the incidence of SGA, low birth weight or preterm birth was 40.3% (N=494) ([name], personal communication). Therefore the study is designed to detect a 25% difference between 40.3% in the control (IPTp) group and 30.2% in the intervention (ISTp) group.

This would require 491 participants in each arm or 982 in total. To allow for a 15% loss to follow-up, 1155 women in their first and second pregnancies will be recruited. This sample size would also have an 81% power to detect a 25% or greater reduction in placental malaria (active or past infection), with a significance level of 0.05. If a power of 80% is used, the study can detect a difference of 21.8% or greater in the primary endpoint. If the incidence is 33.3% instead of 40.3% the study still has 80% power (instead of 90%) to detect a 25% reduction.

The trial is also designed to detect a 50% reduction in past or present placental malaria infection at delivery in multigravidae, based on previous studies of IPTp, assessed by placental histopathology and RDT. The current rate in women in Malawi who are taking IPTp-SP is estimated from IPT-mon at 20.5% ([name], personal communication). A reduction by 50% to 10.25% will require 213 women per arm or 426 in total. To allow for a 15% loss to follow-up we will recruit 500 multigravidae.

The total sample size will therefore be  $1155 + 500 = 1655$ .

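### The planned total of 1,665 women does not match its own strata (1155 + 500 = 1,655), and the 776 women expected in the ISTp arm fit neither total

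*Combined protocol and SAP*

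**What the plan says.** All the figures are in current text of the combined protocol and SAP.

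- **Synopsis (section 3):** planned sample size 1,665.
- **Section 7.1:** "The study requires 1665 women overall, including 1155 primi and secundigravidae and 500 multigravidae".
- **Section 17.1, first and second pregnancies:** "This would require 491 participants in each arm or 982 in total", then "To allow for a 15% loss to follow-up, 1155 women in their first and second pregnancies will be recruited".
- **Section 17.1, multigravidae:** "A reduction by 50% to 10.25% will require 213 women per arm or 426 in total", raised to 500 for the same 15% loss.
- **Section 17.1, total:** 1155 + 500 = 1655.
- **Section 17.2:** two randomization sequences, one per gravidity group, allocated 1:1.
- **Section 7.2.11:** "Around 776 participants in this trial will receive ISTp". The section expects 20% to 30% of these women to be treated with DHA-PQ, hence 155 to 233 exposed women.

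**The concern.** The sentence in section 7.1 contradicts itself: the total it gives is 10 more than the two groups it lists. There is no third stratum to hold the difference, because section 17.2 generates sequences for two gravidity groups only. The same wrong total is the headline figure in the synopsis, where most readers will look for it and from where it is likely to be copied into reports. Section 17.5 commits the trial to CONSORT reporting, which needs a single planned number.

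The ISTp-arm count in section 7.2.11 is a second mismatch. With equal allocation, the arm should be half of the total, and 776 is half of neither 1,665 nor 1,655. The section uses the exposure derived from it to support its statement that sub-clinical effects cannot be analysed meaningfully, so the count should follow from the design.

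**Working it through.** **1. Are the stratum sizes sound?** This shows which total the design supports.

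The formula is the usual two-proportion one with pooled variance under the null, followed by the continuity correction:

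n = [z(α/2)·√(2·p̄·q̄) + z(β)·√(p1·q1 + p2·q2)]² / (p1 − p2)²

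n' = (n/4)·[1 + √(1 + 4/(n·|p1 − p2|))]²

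*First and second pregnancies.* Section 17.1 specifies the test "with an 90% power and a 2-sided significance level of 0.05" and the rates as follows: "the study is designed to detect a 25% difference between 40.3% in the control (IPTp) group and 30.2% in the intervention (ISTp) group".

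- With p1 = 0.403 and p2 = 0.75 × 0.403 = 0.30225, n = 471 without and n' = 491 with the continuity correction. The plan's 491 is reproduced. Using the rounded 30.2% gives 488.
- 2 × 491 = 982, and 982/0.85 = 1155.3. The plan's 1155 is reproduced.

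*Multigravidae.* The control rate is 20.5% and the target 10.25%. Section 17.1 gives no power for this stratum, so 80% is assumed.

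- n = 194 without and n' = 213 with the correction. The plan's 213 is reproduced. At 90% power the corrected figure would be 278, so the plan's number points to 80%.
- 2 × 213 = 426, and 426/0.85 = 501.2, against 500 in the plan. This is a rounding difference.

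**2. The total.**

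- Sum of the printed strata: 1155 + 500 = 1,655.
- Printed in the synopsis and section 7.1: 1,665. Difference: 10, and 10/1,655 = 0.6%.
- Rounding does not explain it. The unrounded strata give 1155.3 + 501.2 = 1,656.5, and rounding each up gives 1156 + 502 = 1,658.

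**3. The ISTp arm at 1:1.**

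| Basis | Women in the ISTp arm |
|---|---|
| 1,655 / 2 | 827.5 |
| 1,665 / 2 | 832.5 |
| Evaluable, 491 + 213 | 704 |
| 0.85 × 827.5 | 703 |
| Section 7.2.11 | 776 |

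The figure 776 implies a total of 2 × 776 = 1,552, which appears nowhere in the documents. It is 51.5 below 827.5 (51.5/827.5 = 6.2%) and 56.5 below 832.5 (6.8%). It lies above the evaluable arm, so loss to follow-up does not produce it either.

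**4. DHA-PQ exposure at 20% and 30%.**

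- On 776: 0.20 × 776 = 155.2 and 0.30 × 776 = 232.8. The plan's 155 to 233 is correct arithmetic on its own base.
- On 827.5: 0.20 × 827.5 = 165.5 and 0.30 × 827.5 = 248.3, so about 166 to 248.
- Difference: 10.3 women at the lower end and 15.5 at the upper end.

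**The case against.** The strongest reply is that nothing in the design depends on either slip. Recruitment targets are set by stratum in section 17.1, each gravidity group has its own randomization sequence, and 1155 and 500 agree between sections 7.1 and 17.1. This stands: power and stratum targets are untouched.

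Section 7.2.11 also marks its counts as approximate, and the placental-infection estimate it quotes has a 95% confidence interval of 19% to 42%. Against that uncertainty a 6% shift in the base is minor, and the two exposure ranges largely overlap. The section compares its exposure with 860 women scheduled for DHA-PQ in another trial, and 10 to 15 more women do not alter that comparison. This stands too. It does not explain why the base is 776 when the allocation gives about 828.

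The count might be meant as women who actually start the intervention. About 52 of 828 would then have to leave before their first screening, which takes place at the enrolment visit. Section 17.3.1 mentions only a few same-day withdrawals, judged by other trials. The documents therefore do not support this explanation, though they do not rule out some unstated basis.

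Some stronger readings are tempting and should not be drawn:

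- **Recruitment and the interim.** A reader might infer that the wrong total shifts the end of recruitment or the interim analysis. Section 17.4 places the interim half-way without naming a count, and no section ties the end of recruitment to 1,665. Even if half the total were meant, the change is 832.5 − 827.5 = 5 women. The same five women would be at issue in the section 7.1 option to add sites if recruitment is slow.
- **Fixing interim counts here.** Half of 1155 and 500 (578 and 250) is half of the women recruited, and 578/982 and 250/426 are both about 59% of the planned evaluable women. What the interim should count is a separate design decision that does not follow from a summation slip.
- **Registration.** Whether a registry carries the wrong figure cannot be judged from the documents.

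**Conclusion.** The point holds as an error in stated figures with small consequences. The total of 1,665 in the synopsis and section 7.1 is wrong by 10 women (0.6%). This is certain, because the total is a plain sum of two printed integers, and section 17.1 gives the correct sum. The 776 in section 7.2.11 is about 6% below the arm size implied by 1,655 and 1:1 allocation, and DHA-PQ exposure is understated by about 10 to 15 women.

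The figures of about 828 and about 166 to 248 assume that every allocated woman is counted and that the plan's 20% to 30% treated fraction applies. The documents do not say how 776 arose, so it may have a basis that is not shown. A reader might infer that the trial is mis-sized or that the safety argument fails. Neither follows: the stratum sizes reproduce (with 80% power assumed for multigravidae), and exposure remains too small for the analysis that section 7.2.11 declines to make.

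**What to change.** 1. In the synopsis and in section 7.1, change 1,665 to 1,655, to agree with section 17.1.
2. In section 7.2.11, replace 776 with about 828 and the exposure range with about 166 to 248, or keep 776 and state its basis.

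The cost is wording only. No stratum target, power statement, endpoint, analysis or procedure changes.

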## 7.3 Rationale for design

### 7.2.1 Design as a superiority trial

ISTp will be more complex to implement and potentially more expensive than IPTp and, unlike with IPTp, sub-patent infections will not be prevented or suppressed, thus concomitant use of ITNs is important. Countries with moderate transmission would only consider switching to a new strategy if it is clearly superior to the current policy of IPTp-SP, either because SP is failing or because SP is potentially harmful.

### 7.2.2 Study of efficacy versus effectiveness

This trial is designed primarily to assess the efficacy of ISTp when implemented as intended. This proof of concept is needed as a logical step before further assessments of effectiveness in practice are undertaken, as it has not yet been established in this context. In addition, as any effect will usually tend to be greater under conditions of optimal implementation, the sample size required is smaller for an efficacy trial than for an effectiveness trial. Therefore efforts will be made to maximise participant adherence to the study protocol, including telephone reminders to women to take their DHA-PQ as prescribed, and active follow-up of participants who miss scheduled appointments.

However, some attempts will be made to assess the potential effectiveness of ISTp in practice. Data will be collected to assess the tolerability of the intervention and levels of adherence under the trial conditions.

